### 2.5. Sample Size Calculation

Sample size has been estimated using G*Power software (version 3.1.9.7), considering the clinical rating scales described above as outcome measures of the study. Based on previous literature on BD youths treated with lithium [50], the YMRS score was the best available measure to determine the effect size that would be worth testing and thus was taken as the reference. The calculation was based on a repeated measures test between two independent mean differences of the main outcome, establishing the error level at 0.05, power at 0.95, and effect size at 1.06. Based on this setting, a sample size of 40 subjects (20 patients with ASD-BD and 20 BD-only controls) was obtained. However, since a dropout rate of 20% is expected after 6 months of follow-up based on our previous studies, 5 additional participants per group will be recruited, leading to a total number of 50 subjects as the final sample size (25 patients with ASD-BD and 25 BD-only controls).

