The association between ASD and BD in adult subjects has been repeatedly confirmed, and lithium has been suggested as the first treatment option for high-functioning ASD with comorbid BD [33]. Similarly, children and adolescents with ASD have high rates of comorbid BD, up to 4–7% in clinical cohorts [34,35], and often experience irritability, aggression, self-injury, and tantrums, as well as subclinical manic symptoms including elation, expansive mood, and racing thoughts [32]. Also, it is increasingly recognized that comorbid BD significantly contributes to the morbidity associated with ASD [36], although the communication difficulties and the frequently low intellectual functioning complicate the identification of comorbid clinical pictures in this population [37]. To further increase this clinical complexity, BD in ASD is often characterized by atypical features, such as irritability and behavioral disturbances, which are frequently associated with several other potentially comorbid conditions, including, above all, ADHD [37,38]. Finally, suicidal behaviors are also frequently observed in ASD-BD patients and may confer a greater risk of hospitalization [39,40] since ASD is an independent risk factor for suicide, with a probability to die by suicide which is ten times greater than in the general population [41].

Despite these considerations, research so far has only scarcely targeted this comorbid population to define guidelines for the clinical management of associated morbidity. Pharmacological treatment options available for ASD with comorbid BD are not directed to the core symptoms of the disorder but rather target challenging behaviors associated with comorbidities [32]. Second-generation antipsychotics (SGAs)—i.e., Risperidone and Aripiprazole—are currently approved by FDA and EMA for treating irritability and aggression in ASD youths [42]. Approximately 65% of ASD-BD patients treated with SGAs showed an improvement greater than 30% in irritability, and despite an atypical severity of BD symptoms in ASD youths, the presence of this comorbidity does not impact the relative rate of response [43]. However, given the high risk of SGA-related side effects, including weight gain and metabolic disorders, increased serum prolactin, and sedation, antipsychotics should be used cautiously [32].

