On the other hand, lithium has been rarely studied in children with ASD, despite its established efficacy in controlling mood disorder symptoms in the neurotypical population, and controlled trials supporting its efficacy for mood instability, impulsivity, and cyclicity in ASD subjects are lacking. However, some case reports [44,45,46] and two retrospective chart reviews are available for this purpose [47]. In the first of these latter [48], 43% of ASD patients who received lithium improved after treatment, along with 71% of those who had two or more pretreatment mood disorder symptoms including mania and euphoria. In the second [49], 73.7% of patients with ASD experienced significant clinical improvement after add-on lithium salts to their treatment regimen, thus representing a reliable alternative to antipsychotics and other psychotropic medications.

Thus, the present article will present the research protocol for a longitudinal prospective study aiming to assess the efficacy and tolerability of Extended-Release Lithium Salts treatment in adolescents with ASD and comorbid BD versus neurotypical BD patients. This naturalistic comparative study will specifically focus on BD-related morbidity often associated with ASD, including suicidality, non-suicidal self-injury, irritability/emotional dysregulation (ED), and aggression in a longitudinal sample of referred youths with BD with and without ASD. In the absence of previous research on this topic, we hypothesize the non-inferiority of Extended-Release Lithium Salts in adolescent patients with BD and ASD compared with those without comorbid ASD.

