## 3. Discussion

The present study seeks to address a significant gap in the literature regarding the efficacy and tolerability of Extended-Release Lithium Salts in adolescents with Bipolar Disorder and comorbid Autism Spectrum Disorder. Lithium, widely recognized for its effectiveness in treating BD in the neurotypical population [1,2], has been insufficiently studied in individuals with ASD, particularly in youth populations [32,48,49]. The inclusion of Extended-Release Lithium Salts as a treatment modality in this population is a critical step toward understanding its potential benefits and limitations in this specific comorbid condition.

The longitudinal prospective design of the present study allows for a comprehensive assessment of both efficacy and safety, providing valuable insights into the clinical management of BD in ASD. By focusing on key outcome measures such as mood instability, suicidality, irritability, and aggression, which are prevalent in this population [32,41], the study aligns with the clinical challenges often observed in ASD-BD patients. The inclusion of a well-matched control group of neurotypical BD patients, in which lithium efficacy has been already established [1,2], further strengthens the study capacity to discern the specific effects of Extended-Release Lithium Salts in the context of comorbid ASD.

Another strength of the study is its naturalistic approach, which reflects real-world clinical settings and may enhance the generalizability of the findings. Additionally, the thorough assessment procedures, including the use of validated diagnostic tools and clinical rating scales, ensure a robust evaluation of both primary and secondary outcomes. The careful consideration of covariates, such as age, gender, and concurrent psychotropic treatments in the statistical analysis, will allow for a more nuanced understanding of the factors influencing treatment outcomes. Finally, the sample size calculated to achieve sufficient power will provide further statistical robustness.

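### The 1.06 effect size behind the stated 95% power has no support as an ASD versus non-ASD difference or as a non-inferiority margin, and the sidedness of the test is not stated

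*Protocol article*

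**What the plan says.** Section 2.5 of the protocol article describes a repeated-measures comparison of two independent mean differences in the main outcome, computed in G*Power, "establishing the error level at 0.05, power at 0.95, and effect size at 1.06". The result is 40 patients, 20 per group, raised to 25 per group for 20% dropout. The metric of the effect size and the sidedness are not given.

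On the origin of the value, the same section says: "Based on previous literature on BD youths treated with lithium [50], the YMRS score was the best available measure to determine the effect size". It describes the value as one worth testing.

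The Introduction sets out the study question: "In the absence of previous research on this topic, we hypothesize the non-inferiority of Extended-Release Lithium Salts" in patients with comorbid ASD relative to those without. Section 2.6 plans multiple linear regression to detect an effect of the ASD diagnosis on score changes, also without stating sidedness. The Discussion lists as a strength that "the sample size calculated to achieve sufficient power will provide further statistical robustness".

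**The concern.** Two things in the calculation do not fit the question that the study asks.

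First, the 95% figure depends on a choice that is not declared. For the comparison described, 20 per group is the minimum for a one-sided 5% test. The regression wording in Section 2.6 speaks of detecting an effect, which most readers would take as two-sided.

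Second, and more important, the effect size was carried from one contrast to another. A YMRS value from lithium-treated bipolar youths says something about such patients under lithium. The study compares two groups who both receive lithium and differ in ASD diagnosis. By the authors' own account ("In the absence of previous research on this topic"), there was no earlier evidence on that comparison, so 1.06 cannot be an observed ASD versus non-ASD difference, and no reason is given for using it as one.

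What is at stake is how a null result will be read. With high power claimed as a strength, a non-significant ASD coefficient invites the conclusion that lithium works as well in ASD. The Conclusions section intends the findings to guide practice in a vulnerable group. A design sized for a difference above 1 SD cannot exclude smaller but still sizeable deficits.

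**Working it through.** **Inputs.** From Section 2.5: error level 0.05, power 0.95, effect size 1.06, 20 per group with equal allocation, dropout 20%. Assumption: 1.06 is Cohen's d, that is, the between-group difference in mean change divided by its SD.

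**Formula.** Two-sample t-test with n per group: df = 2n − 2 and noncentrality δ = d·√(n/2). Power is the probability that a noncentral t(df, δ) variable exceeds the critical value (for the two-sided test, the negligible opposite tail is added).

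**Reproducing the plan's figure.** n = 20 gives df = 38 and δ = 1.06 × √10 = 3.35.

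| Analysed per group | One-sided 5% | Two-sided 5% |
|---|---|---|
| 19 | 94.1% | 88.9% |
| 20 | 95.0% (0.9502) | 90.4% (0.9043) |
| 24 | 97.6% | 94.9% |
| 25 | 98.0% | 95.7% |

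The one-sided test reaches 95% first at exactly 20 per group, which matches the article. The two-sided test needs 25 analysed per group. The dropout step is correct: 20/0.8 = 25 enrolled per group. Those 25 would meet a two-sided 95% target only if nobody dropped out.

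**Other routes to 40.** A between-factor repeated-measures ANOVA with f = 1.06/2 = 0.53 has noncentrality f²·N·m/(1 + (m − 1)ρ), for m measurements with correlation ρ. It also gives N = 40 when ρ = 0.6 with two measurements or ρ = 0.7 with three. With ρ = 0.5 it gives 38 and 34. The article states neither a conversion to f nor a correlation, and that test compares average levels, not mean changes. So the one-sided t-test is the simplest reconstruction of the wording, but not the only setting that gives 40.

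**Read as non-inferiority.** Suppose the true difference is zero, the margin is M (in SD units) and the test is one-sided at 5%. The power formula is the same with M in place of d. Twenty per group gives 95% power when M = 1.06. On this reading, the ASD group could change by about one SD less than the comparator and still fall inside the margin.

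**What 20 per group delivers for the ASD contrast (two-sided 5%).** The differences below 1.06 are illustrations and are not taken from the article, except that 0.91 is solved for 80% power.

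| Between-group difference (SD) | Power |
|---|---|
| 1.06 | 90% |
| 0.91 | 80% |
| 0.8 | 69% |
| 0.5 | 34% |
| 0.3 | 15% |

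**Precision.** The 95% CI half-width for the difference in mean change is t(0.975, 38) × √(2/20) = 2.024 × 0.316 = 0.64 SD.

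**The case against.** **Non-inferiority is normally tested one-sided.** A one-sided 5% calculation could therefore be what the authors intended, and two-sided defaults in software prove nothing about the plan. This stands, and it is why the two-sided figure alone is not the main point. It does not rescue the calculation, because 1.06 SD then becomes the margin without being named or justified as one.

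**The sidedness gap is small.** It is under five percentage points, power at 1.06 SD stays above 90%, and one added word would settle it. This also stands.

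**The authors call 1.06 an effect worth testing, not an expected ASD difference.** That is fair, and they do name its source. The article still gives no reason why a value from lithium-treated bipolar youths is the difference worth testing between ASD and non-ASD patients.

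**Stronger readings that the article does not support.** A reader might infer that no repeated-measures setting can give 40. The working shows that some can. A reader might also infer that the design supposes ASD patients lose an amount as large as the whole lithium effect. That needs reference 50, which is not available here; 1.06 could be a pre-post change, a difference from a comparator, or something else. Finally, the Introduction's remark that "the presence of this comorbidity does not impact the relative rate of response" concerns antipsychotics and irritability. It is weak evidence about lithium and YMRS change, and the point does not rest on it.

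**Conclusion.** The point holds in this form. The stated 95% power can be reproduced, most simply as a one-sided 5% two-sample t-test that is not declared; two-sided power is 90.4%, a minor shortfall. The substantive defect is that 1.06 is unsupported both as an ASD versus non-ASD difference and as a non-inferiority margin. The claim of sufficient power therefore does not hold for the study's own question. With 20 analysed per group, the two-sided design detects 0.91 SD with 80% power and estimates the difference to within about ±0.64 SD.

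This rests on reading 1.06 as Cohen's d and on a t-test of mean change between independent groups. It does not show that the sample is too small for a 1.06 SD difference, and it is not a call for more patients. The article's condensed form does not excuse it, because the inputs, the result and the power claim are all stated there.

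**What to change.** Change text only and keep 25 enrolled per group.

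1. In Section 2.5, state the test used in G*Power, the metric of 1.06 and whether the 5% level is one- or two-sided. If a repeated-measures procedure was used, give the number of measurements and the assumed correlation.
2. State that 1.06 comes from lithium-treated bipolar youths and is neither an expected ASD versus non-ASD difference nor a justified non-inferiority margin.
3. Restate what the sample offers: 20 analysed per group gives 90% power (two-sided 5%) for a between-group difference of 1.06 SD, 80% for 0.91 SD and, as an illustration, 34% for 0.5 SD. The 95% CI half-width is about 0.64 SD for the difference in change.
4. Say that a non-significant ASD effect will not be read as non-inferiority.
5. In the Discussion, remove the statement that the sample size gives sufficient power.

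The cost is a less favourable power statement. No extra patients, visits or measurements are needed.

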### 2.6. Statistical Analyses

Statistical analysis will be performed using RStudio^®^ (version 1.3.1093, RStudio, PBC, Boston, MA, USA). Non-parametric tests for repeated measures (e.g., Wilcoxon signed rank test) will be used to analyze the psychiatric assessment score variations of the clinical rating scales described above. Additionally, multiple linear regression models will be performed to detect the effect of the ASD diagnosis on the variations on patients’ clinical scores. Patients’ age and gender, ongoing treatment with other psychotropic drugs, and lithium plasma levels will be considered as covariates in multivariate analyses to account for possible specific effects.

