### 2.2. Recruitment

Patients will be consecutively enrolled after assessment at our hospital for eligibility. Those who meet the eligibility criteria listed below will be included following a thorough clinical screening. All participants and their caregivers will be informed about the assessment procedure, and participation in the study will be voluntary. Recruited patients and their parents will be asked to provide their signed informed consent. Additionally, patients will be allowed to withdraw their consent any time during the study.

Inclusion criteria will be as follows: lithium-naïve adolescent inpatients or outpatients aged 12 to 18 years; informed consent obtained from the patient and both caregivers; diagnosis of Bipolar or Related Disorders (Bipolar Disorder type I (BD-I), Bipolar Disorder type II (BD-II), Cyclothymic Disorder, Other Specified or Unspecified Bipolar Disorder) with or without a diagnosis of Autism Spectrum Disorder according to the Diagnostic and Statistical Manual of Mental Disorders, Fifth Edition, Text Revision (DSM-5-TR); cognitive functioning within the borderline to normal range (i.e., Full-Scale Intelligence Quotient (FSIQ) or General Ability Index (GAI) ≥ 70); current presence of Self-Injurious Thoughts and/or Behaviors (SITB) (i.e., including non-suicidal self-injury (NSSI), intentional self-harm, suicide ideation, plans or preparations, or suicide attempts) as assessed through clinical interview (i.e., investigated by administering the Columbia—Suicide Severity Rating Scale); current presence of Emotional Dysregulation (ED) and/or irritability as assessed by means of standardized clinical measures (i.e., Reactivity, Intensity, Polarity, and Stability questionnaire for Youth and/or Affective Reactivity Index above the clinical cutoff). These latter criteria will be considered to ensure a relatively high clinical severity of the included sample.

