### 2.3. Procedure and Assessment

A matching number of BD patients with and without comorbid ASD will be recruited. The ASD-BD group will be the experimental arm of the study, with the BD-only group as the clinical comparator. Both groups will be followed up for six months after recruitment while receiving treatment with Extended-Release Lithium Salts for clinical indication. Primary and secondary outcome measures will be acquired before treatment initiation (T0), as well as three (T1) and six (T2) months after reaching stable drug dosage (Steady State—SS). At T0, patients will be screened for eligibility and carefully evaluated by means of the following diagnostic tools: the semi-structured DSM-5-based clinical interview Kiddie Schedule for Affective Disorders and Schizophrenia—Present and Lifetime version (K-SADS-PL); the Wechsler Intelligence Scale for Children—fourth edition (WISC-IV); the Autism Diagnostic Observation Schedule—second edition (ADOS-2); and the Autism Diagnostic Interview—Revised (ADI-R).

At each timepoint (T0, T1, and T2), patients will be thoroughly assessed as for clinical routine. The following rating scales will be filled in by clinicians based on parents’ and caregivers’ reports: the Clinical Global Impression (CGI) scale scores and the Children Global Assessment Scale (CGAS) scores. Patients will be also administered the following clinical interviews: the Children Depression Rating Scale (CDRS); the Young Mania Rating Scale (YMRS); the Columbia—Suicide Severity Rating Scale (C-SSRS); the Deliberate Self-Harm Inventory (DSHI); Reactivity, Intensity, Polarity and Stability questionnaire for Youth (RIPoSt-Y). Caregivers will be administered the following clinical rating scales: the Modified Overt Aggression Scale (MOAS) and the Affective Reactivity Index (ARI).

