## 4. Conclusions

This study will have the potential to make a significant contribution to the field. By investigating the efficacy and safety of Extended-Release Lithium Salts in a previously under-investigated population, it may provide critical evidence to guide clinical practice and inform future research. The study findings could pave the way for more personalized treatment approaches for adolescents with BD and comorbid ASD, ultimately improving outcomes for this vulnerable population. Specifically, if the results show that lithium offers advantages over harmful BD-related outcomes in youth with ASD, such as suicidality, while maintaining a manageable side effect profile, our study will assist clinicians in considering this often overlooked treatment option for this highly vulnerable group.

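### Within-patient tests of change cannot show lithium efficacy: entry selects for current severity on the T0 assessment that is also the baseline for RIPoSt-Y, ARI and C-SSRS, and everyone receives lithium

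*Protocol article*

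**What the plan says.** **Analysis.** Section 2.6 gives two analyses. The first is a test of change within patients: "Non-parametric tests for repeated measures (e.g., Wilcoxon signed rank test) will be used to analyze the psychiatric assessment score variations". The second compares the groups: "multiple linear regression models will be performed to detect the effect of the ASD diagnosis" on change in the clinical scores, with age, gender, other psychotropic drugs and lithium plasma levels as covariates. The baseline score is not among the listed covariates.

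**Entry.** Section 2.2 requires current self-injurious thoughts or behaviours, "investigated by administering the Columbia—Suicide Severity Rating Scale". It also requires current emotional dysregulation and/or irritability, defined as "Reactivity, Intensity, Polarity, and Stability questionnaire for Youth and/or Affective Reactivity Index above the clinical cutoff". The purpose is stated: "These latter criteria will be considered to ensure a relatively high clinical severity of the included sample".

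**Baseline.** Section 2.3 makes the screening visit the baseline visit: "At T0, patients will be screened for eligibility and carefully evaluated". The C-SSRS, RIPoSt-Y and ARI are then repeated at T1 and T2. The Abstract lists suicidality and emotional dysregulation among the primary outcomes.

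**Comparator and claims.** Both groups receive extended-release lithium (section 2.3). Section 2.1 calls efficacy the primary aim. The Discussion says that the BD-only group "further strengthens the study capacity to discern the specific effects of Extended-Release Lithium Salts" in the context of comorbid ASD. The Conclusions foresee guidance to clinicians "if the results show that lithium offers advantages over harmful BD-related outcomes in youth with ASD", with suicidality as the example.

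**The concern.** A signed-rank test of T0 against T1 or T2 has no change as its null hypothesis. Patients admitted because they are currently severe on a scale will on average score lower when measured again, even on an inert treatment. Part of the T0 score is transient, and mood episodes also resolve with time. The null can therefore fail without any drug effect.

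Since every patient takes lithium, neither group shows what would have happened without it. The regression in section 2.6 estimates how ASD modifies change under lithium; it does not estimate what lithium does.

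At stake is how a significant within-group fall is read. Under an aim worded as efficacy, and with claims about specific effects and advantages, it could pass as evidence that lithium works in adolescents with ASD. Suicidality, the outcome that the Conclusions single out, is one of those used for entry.

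**Working it through.** **1. The plan's own figure.** Section 2.5 sizes a comparison of two independent mean differences with effect size 1.06, error level 0.05 and power 0.95, and obtains 20 per group. The noncentral t calculation gives 20 per group with one-sided testing (power 0.9502) and 25 with two-sided testing. So the stated 20 reproduces, as a one-sided figure. The dropout inflation, 20 / (1 − 0.20) = 25 per group, also reproduces. The point here does not rest on a sample-size error. The calculation also shows that the study was sized for the between-group contrast.

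**2. Which outcomes are selected on.**

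| Scale | Used for entry? | Repeated at T1, T2? |
|---|---|---|
| RIPoSt-Y, ARI | Yes, at least one above cutoff | Yes |
| C-SSRS | Yes, used to establish current self-injurious thoughts or behaviours | Yes |
| YMRS, CDRS, MOAS, DSHI, CGI, CGAS | No | Yes |

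**3. Expected change with no lithium effect.** Take a standardised score, entry at T0 above a cutoff c (in SD from the mean of the enrolling population), and retest correlation r. The mean T0 score of those admitted is λ(c) = φ(c) / (1 − Φ(c)), where φ and Φ are the standard normal density and distribution function. The expected change is −(1 − r) × λ(c).

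- c = 0: λ = 0.399 / 0.5 = 0.80; with r = 0.7 the change is −0.3 × 0.80 = −0.24 SD.
- c = +1: λ = 0.242 / 0.159 = 1.53; with r = 0.7 the change is −0.3 × 1.53 = −0.46 SD.

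**4. How often the test declares improvement.** The inputs are n = 20 (section 2.5), zero treatment effect, and a signed-rank test at two-sided 0.05, hence nominally 2.5% in the direction of improvement, with 1,500 simulated studies per cell. The values of c and r are assumptions; the article gives neither. Each cell shows the expected change in SD and the rate of false improvement.

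| Cutoff c (share eligible) | r = 0.5 | r = 0.7 | r = 0.8 | r = 0.9 |
|---|---|---|---|---|
| −1 (84%) | −0.14; 7% | −0.09; 7% | −0.06; 6% | −0.03; 5% |
| 0 (50%) | −0.40; 41% | −0.24; 27% | −0.16; 19% | −0.08; 11% |
| +1 (16%) | −0.76; 94% | −0.46; 75% | −0.31; 56% | −0.15; 30% |

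Section 2.6 does not say whether the test is run by group or on all patients. Pooling would keep the same expected change with more patients, so these rates would rise.

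**5. Scales not used for entry.** Take an outcome with retest correlation 0.7, correlated 0.3 to 0.5 with the entry scale at T0 and 0.2 to 0.4 at follow-up, with the cutoff at the mean (all assumed). The false-improvement rate is then about 3-13%. This covers selection only. Episode resolution is not in the model, and nothing in the design controls for it on any scale.

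**6. The group contrast.** In the same simulations, with both groups selected by one rule and sharing one r, a t-test comparing change between groups rejected in about 3-6% of studies across all settings, against a nominal 5%. That was an unadjusted comparison of change. Adjusting for baseline should not disturb it: given the T0 score, follow-up obeys the same relation in both groups when ASD has no effect.

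**The case against.** **Section 2.6 already contains the right comparison.** This is true. The signed-rank test appears as an example and is not called primary. The hypothesis (Introduction), the aim with versus without ASD (section 2.1) and the sample size are all between-group. A reader might infer that efficacy is tested only by within-group change; the article does not support that. Even so, section 2.6 does not say which analysis carries the efficacy conclusion, and nothing in it stops a within-group p-value from doing so.

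**Selection touches only some scales, and loosely.** This also stands. YMRS, the sample-size reference, is not an entry scale, and neither is MOAS, which measures aggression. RIPoSt-Y and ARI are joined by and/or, so one may be below cutoff, and the C-SSRS criterion is presence, not a score threshold. The single-cutoff model is therefore an approximation. ARI recall covers six months (section 2.4), so at T1 it may reach back before treatment and damp early change.

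**The enrolling population is already severe.** These are diagnosed bipolar patients at a third-level hospital, given lithium for clinical indication. The cutoff may lie at or below their mean, where the rates are 5-41%. It follows that high rates cannot be presumed.

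**The limits are disclosed and the claims hedged.** In part. The Discussion lists non-randomisation and the lack of a control medication, and calls for randomised trials, but it ties these to generalizability. Attribution of change to lithium is a matter of internal validity, and regression to the mean is not named. A reader might infer that the Conclusions already plan to declare an advantage for lithium. They do not: the sentence is conditional. The Discussion phrase about specific effects can likewise be read as the group contrast. The difficulty is that within-group results from this design could not satisfy that condition.

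**BD-only supplies a benchmark of known efficacy.** The Introduction itself reports a lack of evidence for lithium as acute treatment of manic symptoms in adolescents. Moreover, two groups selected by one rule would fall alike with no drug effect at all.

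**Conclusion.** The concern holds in limited form. For RIPoSt-Y, ARI and C-SSRS, a significant within-group fall cannot be attributed to lithium, because the assessment that admits patients is also their baseline and nobody goes without the drug. For the other scales selection acts only indirectly, but their within-group change is uncontrolled as well.

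The direction is clear; the size is not. Depending on where the cutoff lies and on retest correlation, false improvement could be slightly above the nominal 2.5% or could reach 94%. A reader might infer that the study would report efficacy in ASD almost regardless of the truth. That would require cutoffs well above the mean of the enrolling population together with modest reliability, and the article establishes neither.

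The ASD-BD versus BD-only contrast is largely protected, on the condition that both groups are selected by the same rule and have similar retest reliability.

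**What to change.** 1. **Section 2.6:** report within-group change descriptively, as an estimate with a confidence interval, and state that it is not evidence of lithium efficacy. Name the ASD-BD versus BD-only contrast in change, adjusted for the baseline score, as the confirmatory analysis.
2. **Section 2.1:** word the primary aim as the difference in change under lithium between the two groups.
3. **Discussion and Conclusions:** limit statements on lithium's specific effects or advantages to that contrast. Name regression to the mean and the lack of an untreated comparator as limits on internal validity, not only on generalizability.

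The cost is a narrower efficacy claim and the loss of the signed-rank tests as inferential results. No patients, visits or measurements are added.
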